### Power calculation and statistical analyses

The primary outcome of the study is body composition, i.e. fat mass measured by TBW. The body fat mass is on average 2.9 ± 0.6 kg at 12 mo. of age. In order to detect a difference in body fat of 0.24 kg between the intervention (ND) and control groups at 12 mo. of age (α = 0.05, power = 80%) with an attrition of 20%, we will need 125 participants per group.

Comparisons of differences in main outcomes between the ND and control groups will be the focus of the statistical analyses. The primary outcomes will be analysed according to the intention-to-treat principle when comparing the two study groups, but per protocol analyses will also be done. Both parametric and non-parametric tests will be used depending on the distribution of data. Possible effect modifiers and confounders will be included in the analyses as needed to explain group differences. Data on dietary intake will be converted to energy and nutrients through nutrient calculation software (Dietist NET, Kost och Näringsdata AB, Bromma, Sweden).

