**Trial registration:**

NCT02634749. Registration date 18 December 2015.

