## Methods/Design

The overall aim of the study is to compare the effects of a protein-reduced, Nordic diet (ND) portfolio intervention on body composition, metabolic and inflammatory markers, blood pressure, cognitive development, food acceptance and faecal microbiota composition to conventional complementary feeding from 6 to 18 months of age.

More specifically, we will investigate if a complementary diet:Lower in protein (total reduction 30%) from 6 to 18 mo. of age will affect growth, body composition, i.e. reduce total body fat mass and improve metabolic markers, i.e. decrease plasma (P-) levels of insulin, glucose and insulin-like growth factor 1 (IGF-1)Based on Nordic foods from 6 to 18 mo. of age will affect growth, body composition, i.e. reduce body fat mass and improve metabolic markers and the faecal microbiota composition, i.e. a microbiota composition associated with less obesity and inflammationWith a modified fat intake, i.e. a higher intake of long-chain polyunsaturated fatty acids and milk fats, including MFGM will improve body composition, blood pressure, metabolic markers including erythrocyte fatty acid composition, cognitive development and the faecal microbiota compositionWith a systematic introduction of plant foods from the Nordic diet during weaning will increase the acceptance of a larger variety of fruits, berries and vegetables into the diet of the young child at 12 and 18 mo. of age

Primary and secondary outcomes of the study and variables collected on adherence and background factors are shown in Table 1.

**Table 1 Tab1:** Primary and secondary outcomes and adherence and background factors collected the Optimized complementary feeding study

Primary outcomes	
Body composition	Anthropometry (body weight, body length, head circumference) Fat and fat-free mass (deuterium-labelled water)
Biomarkers of metabolic function	P-insulin, P-glucose, P-IGF-1, P-lipids and lipoproteins, P-fatty acids and erythrocyte membrane fatty acids including LCPUFAs (DHA, EPA, ARA), metabolomics (plasma and urine) and lipidomics (plasma), markers of oxidatative capacity, hsCRP
Faecal microbiota composition	Obesity-promoting microflora
Blood pressure	
Secondary outcomes, adherence and background factors	
Dietary intake	
Biomarkers of adherence	Haemoglobin, iron status, P-urea, vitamins C, A, E, carotenoids, folic acid, C15 and C17 fatty acids
Food acceptance	Videotaped test meal
Eating behaviour	CEBQ, CFQ, COC, bitter taste gene *TAS2R38*

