#### Body composition

Total body water (TBW) as a measure of body composition (3 compartments model including total body water, fat and fat-free mass) will be determined at 12 and 18 months of age. TBW will be assessed using deuterium (^2^H_2_O) according to the procedure advised by the International Atomic Energy Agency [54] in collaboration with the MRC Human Nutrition Research Laboratory, Cambridge, UK. A pre-dose urine sample will be collected by placing an absorbent pad (Bastos Viegas, Penafiel, Portugal) in the diaper of the infant. Each infant will then be given an oral weighed dose of deuterium of 1 g/kg. Post-dose urine samples will be collected at home once daily for five consecutive days with dates and times recorded for all samples using absorbent pads as described above, omitting the first urine portion of the day. Each collected pad will be stored at − 18 °C. The pads will then be taken to the Paediatric research facility at Umeå University Hospital, thawed and the urine content extracted using a press, collecting the urine in glass bottles. The glass bottles will be stored at − 20 °C until transported to MRC Elsie Widdowson Laboratory, Cambridge, UK for analysis.

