### Trial status

Recruitment started April 2015 and ended February 2018 with 250 participants included. Data collection will continue until February 2019.

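### The article defines the primary outcome in two incompatible ways: one powered outcome (fat mass at 12 months) in the power section, four whole domains in Table 1

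*Protocol article*

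**What the plan says.** The first paragraph of the section on power and statistical analyses is in the singular: "The primary outcome of the study is body composition, i.e. fat mass measured by TBW". The sample size follows from that one variable at one age: "In order to detect a difference in body fat of 0.24 kg between the intervention (ND) and control groups at 12 mo. of age", with the error rates given as "α = 0.05, power = 80" per cent, 20% attrition and 125 children per group.

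The next paragraph of the same section is in the plural: "The primary outcomes will be analysed according to the intention-to-treat principle when comparing the two study groups".

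Table 1 (Methods/Design) has a primary block with four domains:
- body composition: weight, length, head circumference, fat mass and fat-free mass;
- metabolic biomarkers: insulin, glucose, IGF-1, lipids, fatty acids, and also "metabolomics (plasma and urine) and lipidomics (plasma), markers of oxidatative capacity, hsCRP";
- faecal microbiota composition;
- blood pressure.

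The Abstract names these four domains as the main outcomes. Table 1 gives no ages. The Body composition section says that total body water "will be determined at 12 and 18 months of age".

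**The concern.** A reader cannot tell from the article which result decides whether the trial succeeded. Under the power section it is one comparison. Under Table 1 and the Abstract it is a list containing at least a dozen named measurements, plus omics panels and a microbiota profile. A favourable difference in IGF-1, a lipid fraction or blood pressure could be reported as a positive primary result under Table 1, whereas under the power section it would be a secondary one.

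The error rate and power are stated for fat mass at 12 months only. If the Table 1 list is taken as the confirmatory set, those figures no longer describe the trial-wise chance of a false positive claim, nor the power for any other listed outcome. This matters because the Discussion expects the results to change dietary advice to infants in Sweden and worldwide.

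**Working it through.** **Inputs.** From the power section: difference 0.24 kg, SD 0.6 kg, alpha 0.05, power 80%, attrition 20%, 125 per group. Sidedness is not stated; two-sided is assumed because it reproduces the stated figure. From Table 1: four primary domains. Assumptions not in the documents: one test per domain, each at two-sided 0.05, any single success counted as positive, and the correlation between tests.

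**1. The plan's own sample size.** Standardised difference = 0.24/0.6 = 0.40.

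n per group = 2 × (1.960 + 0.842)² / 0.40² = 2 × 7.85 / 0.16 ≈ 98.1, so 99 evaluable.

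After attrition: 99 / 0.80 = 123.75, so 124, against 125 stated. It reproduces. A one-sided test would give 78 evaluable and 98 randomised per group, which does not match.

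**2. Power as planned.** Completers = 125 × 0.80 = 100 per group. Expected z = 0.40 × √(100/2) = 2.828. Power = Φ(2.828 − 1.960) = Φ(0.868) ≈ 0.807 (0.804 with the t distribution). The 5% and 80% are therefore right for fat mass at 12 months as a single test.

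**3. Family-wise error if Table 1 is the confirmatory set.** With four independent tests: 1 − 0.95⁴ = 0.185. With equally correlated test statistics (simulation, 500,000 draws):

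| Correlation | Family-wise error |
|---|---|
| 0 | 18.5% |
| 0.5 | 15.5% |
| 0.7 | 13.0% |
| 0.9 | 9.3% |

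Every value in this range exceeds 5%.

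**4. Power if alpha is split four ways.** 0.05/4 = 0.0125, critical value 2.498. Power for 0.24 kg with 100 completers per group = Φ(2.828 − 2.498) = Φ(0.331) ≈ 0.630 (0.621 with the t distribution).

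To restore 80%: 2 × (2.498 + 0.842)² / 0.16 ≈ 139.4, so 140 completers, and 140/0.80 = 175 randomised per group, or 350 in total. The Trial status section reports recruitment closed at 250.

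**The case against.** The strongest defence is that the trial has a clear powered comparison and that the article never claims 5% or 80% for the whole of Table 1. That stands. Alpha appears once, attached to fat mass at 12 months, and the arithmetic there is sound. The article is also a condensed account: a multiplicity rule is commonly left to the analysis plan, which is not shown, so its absence here is not a fault. What the defence does not answer is that the word primary is used for two different sets of outcomes. An analysis plan can add a testing rule, but it cannot make both statements true.

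Several stronger readings are tempting, and the documents do not support them.
- *That the stated error rate and power are wrong.* They fail only if Table 1 is read as a confirmatory list with any success sufficient.
- *That both 12 and 18 months are declared primary.* They are measurement times. The only age tied to a hypothesis test is 12 months.
- *That the false-positive risk is far higher,* for example 1 − 0.95²⁰ = 64% for 20 variables. The documents give no number of tests, and independence is not credible here: weight is the sum of fat and fat-free mass, and lipids and fatty acids overlap.
- *That late registration shows the outcome was not chosen in advance.* The article gives "Registration date 18 December 2015" and "Recruitment started April 2015 and ended February 2018 with 250 participants included", so registration did follow the start of recruitment by about eight months. But infants entered at 4–6 months of age. One aged 6 months in April 2015 reached 12 months in October 2015 and 18 months in April 2016. Registration therefore preceded every 18-month measurement, and could follow 12-month measurements only in the earliest recruits. The registered outcome is not shown, so the dates settle nothing either way.

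**Conclusion.** The point holds as an internal contradiction. The power section names and powers one primary outcome; Table 1 lists four primary domains, the Abstract repeats them as main outcomes, and the analysis paragraph reverts to the plural. The stated alpha and power apply to fat mass at 12 months and to nothing else in the list.

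The cost of leaving Table 1 as it stands is conditional. It rests on one test per domain at two-sided 0.05, any success counted as positive, and no adjustment; none of these is stated in the article. On that basis the family-wise error is about two to four times the nominal 5%. Protecting it by an equal split would cost roughly 18 percentage points of power for the planned difference, and the closed sample cannot recover them. Testing individual biomarkers or omics features would add to the number of tests, but by how much cannot be derived from the documents.

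**What to change.** Make Table 1, the Abstract and the power section state the same single primary outcome: the between-group difference in fat mass (kg, by total body water) at 12 months. This is the only comparison that the closed sample of 250 was sized for. Relabel fat mass at 18 months, anthropometry, fat-free mass, the biomarkers and omics panels, microbiota and blood pressure as secondary or exploratory, and put the plural in the analysis paragraph into line. Lock the change before any data are compared by group.

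If the investigators prefer to keep several primary outcomes, the article should instead state which variables and ages they are, how the overall error is controlled, and what power remains at 250 participants.

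The first option needs only wording: no further participants, visits or samples. Its downside is that fewer results can be presented as primary.

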### Randomisation, blinding, coding and data management

The participants will be randomized at recruitment to either the Nordic diet (ND, intervention) or the Regular (control) group (Fig. 1). Group affiliation will be blinded for participating families and the researchers. Boys and girls will be randomised separately in blocks of 10 from a pre-printed, computer-generated list available to the research nurses, who will enter in participants consecutively. Each participant will be given a unique study identification number. The identification number together with the date of birth will serve as identification on all forms, questionnaires, measurements and as participant identifier in the study database. The key identifying each individual with the unique identification number will be kept in a locked safe to which only researchers and administrative staff at Paediatrics, Department of Clinical Sciences has access. All data collected will be regarded as confidential and stored electronically in coded format according to the Swedish Personal Data Act (1998:204) and the European Union General Data Protection Regulation (EU 2016/679), but paper copies of forms will be kept as well.

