#### Anthropometry and blood pressure

Anthropometric measurements will be taken at baseline (4–6 mo. of age), 9, 12 and 18 mo. of age at the Paediatric Unit (Department of Clinical Sciences, Umeå University, Umeå, Sweden) by experienced paediatric research nurses in accordance with standardized procedures [53]. Nude weight will be measured to the nearest 0.1 kg with electronic baby scales (Seca 727, Bromma, Sweden). Recumbent length will be measured to the nearest 0.1 cm with a paediatric length board (CMS Weighing Equipment Ltd., London, UK). Head circumference will be measured to the nearest 0.1 cm with non-stretchable tape for infants (Seca 212, Germany). All measurements will be taken in triplicate and the mean value will be recorded.

Blood pressure will be measured with the child sitting in the parent’s lap at baseline (4–6 mo. of age), 12 and 18 mo. of age using a Carescape Dinamap V100 monitor (GE Healthcare AB, Sweden) and age-appropriate blood pressure cuffs.

At baseline, the weight, height and blood pressure of the parents will be measured.

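### The covariate rule can only be applied once group differences are known, and it is not kept apart from the primary comparison; a model fixed in advance should replace it

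*Protocol article*

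**What the plan says.** The section on power and statistical analyses names the main endpoint: "The primary outcome of the study is body composition, i.e. fat mass measured by TBW". It makes the comparison of the two diet groups the focus, by intention to treat, with per-protocol analyses in addition. Two sentences then govern how the comparison is made. The first is "Both parametric and non-parametric tests will be used depending on the distribution of data". The second, which is the subject of this point, is "Possible effect modifiers and confounders will be included in the analyses as needed to explain group differences".

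No covariate is named. The section on randomisation states "Boys and girls will be randomised separately in blocks of 10", so sex is the stratification factor, but the analysis text does not mention it.

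The data-collection sections show what could be used. The infants' weight and length are measured at baseline (4–6 months), and blood pressure and blood samples are also taken then. Total body water, and hence fat mass, is first measured at 12 months, so the primary endpoint has no baseline value of its own.

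**The concern.** In a randomised trial, baseline confounding of the group comparison arises only by chance. Covariates are therefore best chosen in advance because they predict the outcome, not afterwards because they account for a result. The stated rule reverses this order, and that has two consequences.

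First, the analyst may fit several models and has no fixed basis for saying which one is primary. If the choice is influenced by the result, the nominal 5% no longer holds.

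Second, the rule sets no time limit on the covariates. The variables that would best explain a difference in 12-month fat mass include those the intervention is meant to change. Protein intake is to be reduced by 30% by design, and IGF-1 is expected to fall and is listed among the primary outcomes in Table 1. Diet, blood markers and body size are all re-measured after the diets begin. Adjusting for any of these would remove the part of the effect that passes through it.

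The primary effect estimate, on which the conclusion about the diet rests, is what is at stake.

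**Working it through.** **1. The plan's own sample size.** The inputs, all from the power section, are: "The body fat mass is on average 2.9 ± 0.6 kg at 12 mo. of age", so SD = 0.6 kg; a target difference of 0.24 kg at that age; a significance level of 5%; power of 80%; attrition 20%; 125 per group. The test is taken as two-sided.

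n per group = 2 × (1.960 + 0.842)² × (0.6/0.24)² = 2 × 7.85 × 6.25 = 98.1, rounded up to 99. Allowing for attrition, 99/0.8 = 123.75, so 124. The stated 125 is reproduced for an unadjusted comparison. (One-sided, the result would be 78, or 98 after attrition, which does not fit.)

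With 125 × 0.8 = 100 evaluable per group, the standard error is 0.6 × √(2/100) = 0.0849 kg. Power is Φ(0.24/0.0849 − 1.960) = Φ(0.868) = 80.7% (80.4% with the t distribution).

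**2. Cost of choosing covariates after the result.** Simulation under no treatment effect: 200 evaluable infants, 4,000 runs per setting, independent baseline covariates. All subsets are fitted (2² = 4 models for two candidates, 2⁴ = 16 for four), and the smallest p-value for the arm effect is kept.

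| Candidates | Variance explained by each | Smallest p over all subsets | Fixed model with all candidates |
|---|---|---|---|
| 2 | 5% | 8.0% | 5.4% |
| 2 | 10% | 8.0% | 4.5% |
| 4 | 5% | 10.3% | 5.2% |
| 4 | 10% | 13.9% | 4.6% |

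The Monte Carlo standard error near 5% is √(0.05 × 0.95/4000), about 0.3 percentage points, so the fixed model is compatible with 5% throughout.

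**3. Adjusting for a variable on the causal path.** If a share m of a true 0.24 kg difference passes through a variable changed by the diet, a linear model that adjusts for it estimates about 0.24 × (1 − m). The documents give no m, so only the direction can be stated: towards zero.

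**4. If sex were left out.** Simulation of an unadjusted t-test with allocation balanced within sex: 200 infants, 40,000 runs. The variance explained by sex is assumed.

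| Variance explained by sex | Actual type I error | Power, unadjusted | Power, adjusted for sex |
|---|---|---|---|
| 2% | 4.9% | 80.6% | 81.5% |
| 5% | 4.4% | 80.7% | 82.7% |
| 10% | 3.7% | 81.6% | 84.6% |

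The test becomes slightly conservative and gives up about 1, 2 or 3 points of power.

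**5. What a fixed model would bring.** The residual SD is 0.6 × √(1 − R²), entered in the formulas of step 1 with 100 per group. R² is the share of variance in 12-month fat mass explained by the covariates. The documents give no value, so a range is assumed.

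| R² | Residual SD (kg) | Power for 0.24 kg | Detectable difference at 80% power (kg) |
|---|---|---|---|
| 0 | 0.600 | 80.7% | 0.238 |
| 0.05 | 0.585 | 82.7% | 0.232 |
| 0.10 | 0.569 | 84.6% | 0.226 |
| 0.20 | 0.537 | 88.5% | 0.213 |
| 0.30 | 0.502 | 92.2% | 0.199 |

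The formula neglects the few degrees of freedom spent on the covariates, which is immaterial with 200 infants.

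**The case against.** The strongest reply is that this is a condensed article, and that covariate lists and the handling of stratification factors usually belong in an analysis plan that is not shown. For sex and baseline values this stands. A reader might infer that the trial disregards its stratification factor or leaves its baseline measurements unused, but the text is silent on both and excludes neither. Step 4 also shows that leaving sex out would cost a little power and create no false positives.

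The reply does not cover the sentence itself. That sentence is a stated rule, and an unseen plan would have to override it rather than fill it in.

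A second reply is that the sentence speaks of effect modifiers and confounders, and a mediator is neither; it may also refer only to secondary, explanatory analyses. Both readings are possible. A reader might infer that the investigators intend to adjust for protein intake or IGF-1, and nothing in the article says so. The wording permits such adjustment without planning it, and the article draws no line between explanatory analyses and the primary comparison.

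A third reply concerns size. The 8–14% assumes the most favourable model is always reported. The power gain depends on an assumed R² and is close to nil if R² is close to nil, which cannot be excluded because fat mass has no baseline measurement. Both qualifications stand.

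**Conclusion.** The point holds for the covariate rule. As worded, it makes covariate choice depend on the observed group results, does not restrict it to variables measured before the diets begin, and does not keep it apart from the primary intention-to-treat analysis. The worst-case type I error is about 8% with two candidates and 10–14% with four, assuming that each explains 5–10% of the variance and that the smallest p-value is reported. It is an upper illustration, not a prediction.

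The gain in precision from a fixed model is firm in direction, provided the covariates predict the outcome, but its size is not given by the documents: about 81% power at R² = 0 and 83–92% for an assumed R² of 0.05–0.30. It would be wrong to conclude that the trial is underpowered as designed, since the stated 125 per group reproduces without covariates. The data-dependent choice between parametric and non-parametric tests is a separate matter that fixing the covariates does not by itself resolve.

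**What to change.** Before group codes are opened, replace the covariate sentence with the following:

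- **Primary model:** linear regression of 12-month fat mass on arm, sex, baseline weight, baseline length and age at baseline, reporting the adjusted mean difference with its 95% confidence interval. Age belongs in the model because the baseline visit falls anywhere from 4 to 6 months.
- **Blood pressure, and biomarkers with a baseline measurement:** analysis of covariance on the outcome's own baseline value.
- **Everything else:** any further covariate, and any variable measured after randomisation once the diets have begun, only in analyses labelled exploratory.

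If an analysis plan already fixes such a model, state that it takes precedence over the article's sentence.

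The cost is a few lines of wording. The covariates are already collected, and no extra infants or visits are needed. This matters because recruitment has closed at 250 and withdrawals are not replaced. The article reports data collection continuing to February 2019, so on its own timetable the change could be made before the final data were complete.
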